# Effects of football versus aerobic exercise training on muscle architecture in healthy men adults: a study protocol of a two-armed randomized controlled trial

**DOI:** 10.1186/s13063-020-04797-y

**Published:** 2020-12-09

**Keywords:** Muscle architecture, Patellar tendon, Football training, Aerobic training, Isokinetic dynamometer, Passive resisting torque, Randomized controlled trial

## Abstract

**Background:**

Sports and exercise training can attenuate age-related declines in physical function. As people age, they suffer a progressive deterioration of overall muscle structure and function, such as muscle diameter, strength, mass, and power. Therefore, supporting older adults—aged 50 years and above—to continue being physically active is a very important factor. Several forms of exercise (strength, agility, endurance, balance, and flexibility) are recommended. In this regard, football has been repeatedly shown to be an integrative approach to promote measures of strength, endurance, and agility. However, there has been no previous randomized controlled trial that comparatively investigates the effects of football training versus traditional aerobic exercise training on muscle architecture and patella tendon properties in healthy community dwellers. The study protocol is designed to examine whether football differentially affects muscle thickness, muscle length, fascicle length, pennation angle, patella tendon length, and thickness compared to a workload matched traditional aerobic exercise training regimen.

**Methods:**

The study sample consists of 60 untrained but healthy men (50–60 years old), who will be randomly assigned (strata: age, activate) to two groups: football group (*n* = 30) and aerobic group (*n* = 30). The intervention will take place within 12 consecutive weeks, two times a week for 60 min each session. The football group will perform recreational football training as a large-sided game, whereas the aerobic group undergoes a running exercise. Both groups have the same external workload ranging between moderate and high exercise intensity. The outcome measure will be collected before and after the intervention period.

**Discussion:**

Findings of this study will provide insight into the effects of 24 sessions of both football and aerobic training program on the selected groups of men adults, including detecting their effects on the thigh muscle architecture.

**Trial registration:**

DRKS—German Clinical Trials Register, DRKS00020536. Registered on 30 January 2020.

## Administrative information

Note: the numbers in curly brackets in this protocol refer to SPIRIT checklist item numbers. The order of the items has been modified to group similar items (see http://www.equator-network.org/reporting-guidelines/spirit-2013-statement-defining-standard-protocol-items-for-clinical-trials/).

## Introduction

### Background and rationale {6a}

The section is going to introduce a number of points in order: (a) the progressive deterioration aging has on muscles, (b) defining muscle architecture and identifying how training impacts it, (c) highlighting the benefits of football training and aerobic training on aging, and (d) the purpose of the study—to conduct a comparative assessment between the effects football training and aerobic training have on aging, and which one is better.

Besides impaired endurance and balance performance, declines in muscle strength greatly affect the progressive declines in physiological function with age. Good physiological function is maintained until middle age and thereafter progressively deteriorates [26] in the way that the overall muscular strength increased until the age of 30, and remains constant without change until about the age of 50, and then decreased by about 30% between the ages of 50–70 [38]. Also, muscle mass declines by 20 to 50% in humans between the ages of 40 and 80, which is accompanied by a decrease in muscle strength [6, 18]. Moreover, significant reduction of type II fast-twitch fibers is considered highly responsible for the decline in muscle cross-sectional area (CSA) [23]. However, annual strength decline from 50 years of age onwards amounts to 1.4 to 2.5% per year with an increasingly progressive loss of muscle fibers in the limbs [36, 39]. Almost half of the muscle fibers are reported to be lost by the age of 80 [18]. Therefore, middle-aged adults are required to have more physical activity in order to compensate for this continued decline. Adults play sport for a range of health-related and social reasons that can contribute to the experience of successful aging.

In this regard, muscle architecture is considered as an important contributor to the muscles’ overall function. Crucial parameters of muscle architecture include muscle mass, muscle fiber length, pennation angle (PA), and sarcomere length [53]. Also, there are other parameters that can be used in muscle architectural analysis like muscle length (ML), fiber length, and physiological CSA in addition to PA [34]. They play an important role in force generation. Muscle size and force production are strongly influenced by fascicle arrangement (i.e., muscle architecture) within the muscle [4]. Muscle architecture development is associated with running, squat movement, and jumping [25, 27]. Muscle thickness (MT) and PA along with shorter fascicles were beneficial for jumping ability at increased pre-stretch loads [2]. Moreover, training programs like strength training cause several changes to muscle architectures including MT, and these changes were related to relative strength and speed improvements [48].

Sports training plays an important role in the reduction of the age-related progressive deterioration of overall muscle structure and function. For example, 6 weeks of resistance training for older adults is effective at increasing strength, muscle quality, and muscle morphology [52]. Ensuring access to activities that can benefit social health is of great importance to older adults. As sport can provide participation opportunities across generations, it can be an ideal physical activity option for this age group [14]. Moreover, increased physical activity in middle age is probably followed by a reduction in mortality to the same level as seen among men with constantly high physical activity.

Recreational football can be an alternative exercise modality for untrained, healthy, or unhealthy middle-aged and older adults [22]. Football is an effective stimulant of musculoskeletal, metabolic, and cardiovascular adaptations of importance for health and thereby reduces the risk of developing lifestyle diseases [22]. Also, it has effects on various age categories and populations on muscular fitness, health profile, and physical capacity [29]. In this context, aerobic activity is efficient to improve physical fitness and functionality in adults. In fact, maintaining a healthy life would be more appropriate in step-aerobics exercises due to having higher tempos and rhythms than the run-walk exercises [35]. Moreover, aerobic program training can enhance muscle protein, synthesis, irrespective of age [21].

Several studies have recently focused on the effect of resistance or strength training programs on muscle architecture. There are no previous studies that have analyzed the effects of football training program or aerobic training program on muscle architecture, nor there is comparative study between football and aerobic training methods in terms of their effectiveness on muscle architecture. The study protocol is designed to investigate whether football differentially affects muscle architecture, work, power, torque, and patella tendon (PT) compared to traditional aerobic exercise training program in adult men.

### Objectives {7}

The main objective of this randomized controlled trial is to determine the effects of football versus traditional aerobic exercise training on muscle architecture, such as MT, ML, fascicle length (FL), PA, PT length, thigh muscle power, work, and torque. A secondary objective is to examine the effects of both training programs on aerobic capacity and explosive power.

### Trial design {8}

This study is a randomized controlled trial with parallel arms conducted and reported in accordance with CONSORT guidelines for non-pharmacologic treatment.

## Methods: participants, interventions, and outcomes

### Study setting {9}

The measurements will take place at the Departments of Radiology and Physical Therapy at Tishreen University Hospital. The intervention training programs will start from 15 April 2020 until 15 July 2020 in the Latakia’s Sports City Stadium. Sixty untrained men between 50 and 60 years old will be randomly assigned to experimental training groups, either a training group (*n* = 30) following football training program (FG) or a group (*n* = 30) following traditional aerobic training (AG). All participants need to be healthy, without presenting any cardiological, orthopedic, and neurological impairment that can affect testing and training (see inclusion and exclusion criteria for details).

Participants will be asked to complete health and neuromuscular problems or a disease history questionnaire and to provide written approval from their health care provider. The data can arise from two samples of participants where each participant is measured twice before and after an intervention. The measurements used in the protocol will be taken before and after the intervention period (12 weeks). The post-intervention test will be scheduled in the following week, after finishing the 12-week intervention period.

### Eligibility criteria {10}

Inclusion criteria are as follows: (1) healthy adult male volunteers between the ages of 50 and 60 years old, (2) participants must be in good health as determined by screening medical history and physical examination, and (3) they must not suffer from any neuromuscular, cardiovascular, or psychiatric disorder. The International Physical Activity Questionnaire (IPAQ) will be used to measure health-related physical activity in populations. IPAQ has reasonable measurement properties for monitoring population levels of physical activity among 18–65 years old adults in diverse settings [15]. The questions are about the time you spent being physically active in the last 7 days. They include questions about activities you do at work, as part of your house and yard work, to get from place to place, and in your spare time for. The long, self-administered IPAQ questionnaire has acceptable validity [42].

Exclusion criteria are as follows: (1) participants who have a significant history of alcoholism or drug/chemical abuse within the last 2 years; (2) participants with positive results on tests for drugs of abuse or alcohol at screening and check-in; (3) history of unstable psychiatric disorder requiring medications or hospitalization within the previous 12 months; (4) history of a concurrent illness that required hospitalization within 14 days prior to day 1 of the study; (5) any condition that in the clinical judgment of the investigator would make the subject unsuitable for participation; (6) participants who have had a clinically significant illness within 4 weeks prior to day 1; (7) history or current evidence of clinically significant hepatic, renal, cardiovascular (i.e., deep venous thrombosis, pulmonary embolism), psychological, pulmonary, metabolic, endocrine, neurologic (i.e., transient ischemic attack or stroke within the past 6 months), infectious, gastrointestinal (i.e., any condition which may affect drug absorption), hematologic, and oncologic disease, retinopathy, or other medical disorders; (8) history of unexplained syncope; and (9) participants who, in the opinion of the investigator, should not participate in the study.

### Who will take informed consent? {26a}

All participants will be informed of all research protocols and details of the training program, including the applied load intensity. The first author ([name]) will discuss the trial with participants in light of the information provided in the information sheet. We will obtain written consent from patients willing to participate in the trial.

### Additional consent provisions for collection and use of participant data and biological specimens {26b}

On the consent form, participants will be asked if they agree to the use of their data should they choose to withdraw from the trial. Participants will also be asked for permission for the research team to share relevant data with people from the universities taking part in the research or from regulatory authorities, where relevant. The data will be possible for sharing with people from the universities after the permission of participants.

## Interventions

### Explanation for the choice of comparators {6b}

In spite of the increasing numbers of training program research for seniors, many age-related diseases are considered as serious factors that could threaten their health and life. Our research aims to discover the effects of two different training program methods in order to delay the appearance of retraction of muscle properties.

### Intervention description {11a}

The training program will be carried out in two groups at the sports city training stadium (Latakia, Syria), two times a week (60 min per session) on non-consecutive days for more than 12 weeks (24 sessions). Both groups will have the same session load. According to Monoem et al. [37], football players under 18 years old practice small- or large-sided games with the average heart rate that is 155 to 167 beats per minute (bpm) and maximum heart rate (HRMAX) that is between 70 and 90%. To determine training load, the RPE will be obtained using the 10-point Borg scale by having participants rating their training perceived effort 30 min after the end of training according to the procedures suggested by Foster [19].

During the familiarization session, each subject will be given instructions on the use of the RPE scale (Table 1). We will ask the participants to use any number on the scale to rate their overall effort. A rating of 0 indicates no effort (rest), and a rating of 10 indicates maximal effort and associates with the most stressful exercise ever performed. Following each set during the training, the subject will be asked “How would you rate your effort?” We will use the session RPE measure to rate the entire workout (Table 1). A single arbitrary unit representing the magnitude of global TL for each session is then calculated by the multiplication of training intensity and the length of training (min). TL(A.U.) = RPE × session duration (min), where TL is the training load, A.U. is the arbitrary units, and RPE is the rating of RPE.

**Table 1 Tab1:** RPE scale

**Descriptor**	Very easy		Easy	Moderate	Somewhat hard			Hard		Very hard	Maximal
**Rating**	1	2	3	4	5	6	7	8	9	10	

All sessions will include 5 min of warm-up at the beginning of the training session and 5 min cooldown at the end of it, for both groups. The warm-up will focus on pulse-raising, mobility, and preparatory stretching for the conditioning component with joint mobility (starting at the top of the body and working the way down, from the neck, shoulders, upper back, hips, and ankles) and continuous leg movement to facilitate the venous return and coordination exercises (toe-tapping arm circles, heel walks, high knee walk, backward high knee skip). Cooldown will include transition from conditioning component to the stretching phase, which comprises static and dynamic stretching exercises for all major muscle groups. Sessions will be deemed completed when at least 90% of the prescribed exercises have been successfully performed.

Considering that FIFA11+ exercises aim to prevent injury, and that the target group age is between 50 and 60 years old, participants in both groups will perform FIFA 11+ and functional training (4–6) exercises using the major muscle groups with low and moderate intensity in a way that the load did not affect our program goals. Running exercises at low/moderate speed will be combined with planting/cutting movements (5 min). The exercises will be as follows: running exercises (straight ahead, hip out, hip in, circling partner, shoulder contact, quick forwards and backwards) and strength, balance, and agility (sideways bench with leg, vertical hump, jumping box and lateral jumps, across the pitch, running plant and cut bounding, running with toe raise, squats one leg squad, squats walking lunges, hold the ball, single leg test your partner, single-leg throwing the ball with partner, hamstring). Every single exercise has 2–4 sets with 4–8 repletion, with 40 s rest break. At the same time, participants in FG will perform the same training characteristics.

In the main part of the training, we will focus on small game running (20–30–40 m) × 5–10 with 3–5 sets and 1–2 min rest between sets for (AG). Also in the same training load, FG will perform competitive activities like small- or large-sided game or a football match (4 vs 4, 5 vs 5, etc.). All participants in both groups will work in the same/similar conditions and rules. None of the participants will play as a goalkeeper in the FG (Table 2). The level of effort for muscle-strengthening activities should be between moderate and high. On a 10-point scale, where no movement is 0, and maximal effort of a muscle group is 10, the moderate-intensity effort is a 5 or 6 and high-intensity effort is a 7 or 8 (the ACSM guideline recommendations have been considered) Table 2.

**Table 2 Tab2:** Exemplary training programs for the aerobic and football group

Training time	FG	AG	Intensity
5 min	Warm-up	Warm-up	Low
15 min	Injury prevention (FIFA11 ± functional training)	Injury prevention (FIFA11 ± functional training)	Moderate
35 min	Football match (competition activities)	Aerobic training (running)	Moderate to high
5 min	Cooldown	Cooldown	Low

Football players practice small-sided games (3 vs 3, 4 vs 4, 5 vs 5, 6 vs 6) with the average heart rate of 155 to 167 bpm [12]. The intensity of small- or large-sided game is moderate and high (the percentage of HRMAX is between 70 and 85%). Both groups will have the same session load (Table 3).

**Table 3 Tab3:** Training session volume and load

	Time	Sets	Rep	Rest	Effort point scale
Warm-up	5 min				3–4
Injury prevention	15 min	2–4	4–8	40 s	4–5
Main part	35 min	3–5	5–10	1–2 min	7–10
Cooling	5 min	–	–	–	1–2

### Criteria for discontinuing or modifying allocated interventions {11b}

Any participant will be excluded as soon as he gets a serious physically injury or if he is unable to follow up on the training sessions for any other reasons.

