### Concealment mechanism {16b}

Allocation concealment will be achieved using sequentially numbered, opaque sealed envelopes [17]. Participants will be assigned in two intervention groups: a football group and aerobic group in a 1:1 ratio. Allocation concealment will be ensured. The randomization code will not release until the participants have been recruited into the trial, which takes place after all baseline measurements have been completed.

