#### Isokinetic muscular power and work test

The power of knee extensor and flexor muscles will be measured in a sitting position using isokinetic dynamometers (Genu3 Easytech, Florence, Italy). After warm-up exercises, patients perform 4 maximal concentric strokes at an angular speed of 90° per second (knee extension flexion; ROM, 90–0°). Isokinetic tests will be performed when patients have no pain or swelling with ROM more than 120° of flexion with full extension. To ensure maximal effort, 3 to 4 training sessions are allowed before performing the test.

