### Methods in analysis to handle protocol non-adherence and any statistical methods to handle missing data {20c}

#### Regression imputation [24]

Imputation is the process of replacing the missing data with estimated values. Instead of deleting any case that has any missing value, this approach preserves all cases by replacing the missing data with a probable value estimated by other available information. After all missing values have been replaced by this approach, the dataset is analyzed using the standard techniques for a complete data.

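### The rule that excludes men after injury or failure to keep training acts after randomisation and is not reconciled with the plan to preserve all cases

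*Protocol article*

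**What the plan says.** The protocol article, Criteria for discontinuing or modifying allocated interventions {11b}, has one rule: "Any participant will be excluded as soon as he gets a serious physically injury". The same applies to a man who cannot keep up the sessions, whatever the reason. It does not say whether the man leaves the training, the post-test or the analysis.

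Concealment mechanism {16b} places allocation after the baseline tests: "The randomization code will not release until the participants have been recruited into the trial". Any exclusion triggered by training therefore comes after randomisation.

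Section {20c}, whose heading covers protocol non-adherence as well as missing data, describes regression imputation: "Instead of deleting any case that has any missing value, this approach preserves all cases by replacing the missing data" with a predicted value. The completed dataset is then analysed as if fully observed.

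Study setting {9} says "each participant is measured twice before and after an intervention". Table 4 shows this as one baseline assessment and one follow-up assessment. No section says that a man who stops training is still retested.

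Sample size {14} allows 15% dropout among 60 men and does not split it by arm.

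**The concern.** The rule names the participant as the one excluded. Elsewhere the article has separate wording for stopping the exercise: Adverse event reporting and harms {22} speaks of training being discontinued. Someone running the trial from the text as it stands could reasonably drop an injured or non-attending man and not call him back.

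Injury and inability to attend arise during the allocated programme, so they can depend on it. Strategies to improve adherence {11c} links physical collision to games, and in Table 2 only the football arm plays matches in the 35-minute main part. If more men leave one arm, and those who leave would have scored worse, the comparison moves towards men who tolerated football against men who tolerated running. The arm that lost more would then look better than it should.

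Imputation does not clearly repair this. With a single post-baseline measurement, an excluded man who is not retested has only a baseline value. His predicted post-test would come from men who completed and would not reflect his injury or the training he missed, unless these were modelled.

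**Working it through.** **Inputs from the article.** Sample size {14}: pilot means 10.59 (football) and 8.17 (aerobic), SDs 2.80 and 2.01, effect size 0.992, alpha 0.05, power 0.95, minimum 46, raised to 60, dropout 15%. Concealment mechanism {16b}: 1:1 allocation, so 30 per arm.

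**The plan's own figures.**
- Pooled SD = √((2.80² + 2.01²)/2) = 2.437.
- d = (10.59 − 8.17)/2.437 = 0.993, against 0.992 stated.
- A two-sample t test (noncentral t) with d = 0.992 and power 0.95 needs 23 per arm, 46 in all, if one-sided. This matches the stated minimum. Two-sided it needs 28 per arm, 56 in all. The article does not state sidedness.

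**Is loss of power the problem?** 15% of 60 is 9 men, leaving 51.
- With 25 and 26 men, power at d = 0.992 is 0.968 one-sided and 0.935 two-sided.
- With 21 and 30 men it is 0.964 and 0.928.

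Power stays high, so the main issue is bias.

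**Bias if excluded men are deleted.** Let q be the share excluded in an arm, and k the amount, in SD, by which excluded men would have scored below retained men. The mean of all randomised men in the arm is the retained mean minus q × k, so deletion overstates that arm by q × k. With the same k in both arms, the bias in football minus aerobic is k × (qF − qA). The article gives neither q by arm nor k, so the values below are assumptions that keep total loss at 9 men.

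| Excluded, football v aerobic | k = 0.5 | k = 1.0 |
|---|---|---|
| 15% v 15% | 0 | 0 |
| 20% v 10% (6 v 3 men) | 0.10 × 0.5 = 0.05 SD | 0.10 × 1.0 = 0.10 SD |
| 30% v 0% (9 v 0 men) | 0.30 × 0.5 = 0.15 SD | 0.30 × 1.0 = 0.30 SD |

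Reversing the split reverses the sign. The zero in the first row needs the same k in both arms. With 15% lost from each arm but k = 1.0 in one and 0.5 in the other, the bias is 0.15 × (1.0 − 0.5) = 0.075 SD.

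**Scale.**
- Against the planning effect: 0.05/0.992 = 5%, 0.10/0.992 = 10%, 0.15/0.992 = 15%, 0.30/0.992 = 30%.
- In degrees of pennation angle: 0.05 × 2.437 = 0.12 and 0.30 × 2.437 = 0.73.
- Two-sided false-positive rate with no true difference, from the noncentral t with noncentrality b/√(1/n₁ + 1/n₂). For b = 0.10 and arms of 24 and 27, noncentrality is 0.356 and the rate is 0.064. For b = 0.30 and arms of 21 and 30, noncentrality is 1.054 and the rate is 0.179. The nominal rate is 0.05.

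**Sections {11b} and {20c} side by side.** There are three readings of exclusion:
1. Only training stops and the man is retested: the sections agree, but no text provides for the retest.
2. He is not retested but stays in the dataset: {20c} keeps him with a wholly predicted outcome.
3. He leaves the analysis: {20c} is contradicted, and the bias formula applies in full.

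The article does not say which is meant.

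**The case against.** The strongest reply is that {11b} is the section on discontinuing the intervention, so exclusion there may mean only that training stops. Other text points away from deletion: {20c} keeps all cases and covers non-adherence, {26b} asks consent to use the data of men who withdraw, and {22} already has staff document the circumstances when an adverse event ends training. This stands to the extent that a certain contradiction cannot be claimed. It does not remove the point, because no section provides for retesting such men and a post-test that is not taken cannot be recovered later. Nor is this only a detail left to a fuller document: the article states a rule, and states it in a form that permits loss of outcomes.

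A reader might infer that the rule does remove outcomes differentially by arm. The documents do not show this. No injury or stopping rate by arm is given, both arms do the same 15-minute injury-prevention block with jumping and cutting, and the aerobic arm does repeated running efforts. A difference is plausible, but its size and direction are unknown.

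A reader might also count the dynamometer condition, "Isokinetic tests will be performed when patients have no pain or swelling", as a second exclusion. It is a condition for one test, applies to both arms, and removes nobody from the trial or from ultrasound.

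Finally, a reader might measure the bias against a moderate effect of 0.5 SD. That figure is not in the article; the only stated effect size is 0.992.

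**Conclusion.** The point holds as an unreconciled rule that carries a risk of bias. Section {11b} acts after randomisation, is open-ended as to reason, and does not say what happens to the man's follow-up; {20c} promises that all cases are preserved. If these men are not retested, their outcomes are at best predicted from completers.

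Under the assumed splits and an assumed deficit of 0.5 to 1.0 SD, deletion would bias the comparison by 0.05 to 0.30 SD, or 5% to 30% of the planning effect. The upper end needs all nine losses in one arm. The bias is zero if loss and deficit are equal in both arms. The formula models deletion; it does not measure what imputation would leave. The existence of the ambiguity rests on the text alone and needs none of these assumptions.

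**What to change.** Leave the decision to stop training as it is. Reword {11b} so that a man who stops training remains in the trial and is invited to the scheduled post-tests he can safely perform, ultrasound in particular. State that every randomised man is analysed in his allocated arm whatever his attendance, and that the imputation in {20c} is used only for values that could not be measured. Report stopping by arm and reason, including stops that did not follow an adverse event, which {22} does not cover.

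The cost is a change of wording and a few more invitations to visits already planned. Including men who trained little will dilute the estimate somewhat. The result then describes being allocated to football or to running, which is the comparison that randomisation protects.
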